## Abstract

**Background:**

Pressure ulcers (PrUs) are a frequent, serious, and costly complication for veterans with spinal cord injury (SCI). The health care team should periodically identify PrU risk, although there is no tool in the literature that has been found to be reliable, valid, and sensitive enough to assess risk in this vulnerable population.

**Objective:**

The immediate goal is to develop a risk assessment model that validly estimates the probability of developing a PrU. The long-term goal is to assist veterans with SCI and their providers in preventing PrUs through an automated system of risk assessment integrated into the veteran’s electronic health record (EHR).

**Methods:**

This 5-year longitudinal, retrospective, cohort study targets 12,344 veterans with SCI who were cared for in the Veterans Health Administration (VHA) in fiscal year (FY) 2009 and had no record of a PrU in the prior 12 months. Potential risk factors identified in the literature were reviewed by an expert panel that prioritized factors and determined if these were found in structured data or unstructured form in narrative clinical notes for FY 2009-2013. These data are from the VHA enterprise Corporate Data Warehouse that is derived from the EHR structured (ie, coded in database/table) or narrative (ie, text in clinical notes) data for FY 2009-2013.

**Results:**

This study is ongoing and final results are expected in 2017. Thus far, the expert panel reviewed the initial list of risk factors extracted from the literature; the panel recommended additions and omissions and provided insights about the format in which the documentation of the risk factors might exist in the EHR. This list was then iteratively refined through review and discussed with individual experts in the field. The cohort for the study was then identified, and all structured, unstructured, and semistructured data were extracted. Annotation schemas were developed, samples of documents were extracted, and annotations are ongoing. Operational definitions of structured data elements have been created and steps to create an analytic dataset are underway.

**Conclusions:**

To our knowledge, this is the largest cohort employed to identify PrU risk factors in the United States. It also represents the first time natural language processing and statistical text mining will be used to expand the number of variables available for analysis. A major strength of this quantitative study is that all VHA SCI centers were included in the analysis, reducing potential for selection bias and providing increased power for complex statistical analyses. This longitudinal study will eventually result in a risk prediction tool to assess PrU risk that is reliable and valid, and that is sensitive to this vulnerable population.

## Introduction

### Background

The pressure ulcer (PrU) is one of the most significant complications in veterans with spinal cord injury (SCI) in terms of morbidity, mortality, quality of life, and cost of care. The Veterans Health Administration (VHA) has the largest single network of SCI care in the United States providing a full range of care to more than 27,000 veterans. Services by the VHA are delivered through a “hub and spoke” system of care, extending from 24 regional SCI centers, offering primary and specialty care by interdisciplinary teams, to the 135 SCI patient-aligned care teams. These teams are typically comprised of an SCI coordinator (usually a social worker), a nurse, and physician, or support clinics at local VHA medical facilities [1].

The total cost of discharges for veterans with an SCI in the VHA who were discharged from a designated SCI system of care facility (ie, treating-bed section of SCI) with a primary admitting diagnosis of a PrU was over US $300 million for fiscal years (FYs) 2011-2012.  In this time period, veterans with SCI who were discharged from SCI facilities with the primary admitting diagnosis of a PrU—in the International Classification of Diseases, Ninth Revision, Clinical Modification (ICD-9-CM) 707.00-707.09 series—accounted for 64.1% (US $304M/US $474M) of the total costs for SCI discharges in the VHA (Veterans Health Administration, Managerial Cost Accounting System Discharge Pyramid Report, 2015.06.18). Stroupe and colleagues found that the cost of PrU-related hospitalizations for 150 veterans with SCI in the VHA over a 3-year period was approximately US $9 million and total health care costs were US $87,639 higher for patients with PrUs than those without (US $113,579 vs US $25,940, respectively) [2].

Current clinical practice guidelines for PrU prevention and treatment state that all patients should be assessed for risk of developing PrU using a valid, reliable, and sensitive tool [3,4]. The Braden Risk Assessment Scale [5,6], developed to predict risk in general inpatients, is presently used throughout the VHA for inpatients and outpatients. There is often a ceiling effect with most or all persons with SCI being identified at a high-risk level using the Braden Scale. Surveys conducted between 2008 and 2010 by the VHA External Peer Review Program at VHA Spinal Cord Injury and Disorder (SCI/D) Centers found that 91.3% of those measured in SCI were identified as being at high risk for PrU using the Braden Scale.

Reliability and sensitivity have not been fully established for existing tools in persons with SCI [7] despite the unique characteristics of this population (eg, lack of sensation and muscle wasting) [3]. Salzberg and colleagues devised a risk assessment scale specific to the SCI population; although used in a few SCI/D Centers [8], the psychometrics of this tool are limited [9,10].

This 5-year retrospective cohort study will leverage data available in the VHA’s electronic health record (EHR) to develop SCI-specific predictive models that can be used to better identify risk for PrUs. The new model will enable targeted prevention strategies, thereby reducing the burden of this serious complication on veterans, their caregivers, and the health care system.

### Scientific Rationale

Despite widespread implementation of risk assessment tools for PrUs, the incidence of PrUs among veterans with SCI has remained stable. Furthermore, there has been an increase in PrUs in the general population. Data from the Healthcare Cost and Utilization Project (HCUP), and Agency for Healthcare Research and Quality (AHRQ), identified a national increase of almost 80% in PrUs in 2006 compared with 1993; SCI was a frequent comorbidity (29.2%) of those hospitalized with a PrU [11].

In pilot work, we found that the majority of potential PrU risk factors identified in our review were available in the EHR in structured, unstructured, or semistructured data. Structured data, the easiest to extract, are precoded (ie, value or meaning is assigned) and stored in database tables such as the ICD-9-CM codes. Recent studies have shown that it is possible to develop valid risk models based on structured data in the EHR [12-14]. Semistructured data are text formatted into tables, templates, lists, and other documents. Extraction of such data is often difficult because it is commonly embedded within the unstructured clinical narrative and the presentation format is not standardized. Unstructured data are text that is formatted in traditional sentences and paragraphs. It is commonly considered the most difficult data to extract because natural language provides multiple methods of communicating the same essential information.

Recent studies have also shown that natural language processing (NLP) techniques can be used to extract risk and decision-making information from clinical text [15-17]. Natural language processing research focuses on developing computational models for understanding natural language [18]. The specific NLP technique employed varies depending on whether the text is semistructured or unstructured. The NLP techniques are used to extract and encode specifically targeted information in text (ie, information extraction [IE]) and convert it to structured data, which can then be readily used in risk assessment.

### Aims and Hypotheses

The goal of this study is to develop an improved SCI PrU risk model to better predict level of risk, guide preventive practices, and ultimately maximize the patient’s clinical outcomes. The resultant risk model, tailored to veterans with SCI, should promote adoption into clinical practice.

We will test two hypotheses to compare a model based on the commonly used Braden Scale versus (1) a risk model developed using structured data alone and (2) a model using both structured and NLP (ie, semistructured and unstructured) data. A third hypothesis will test the added value of NLP-based data over structured data. The hypotheses are as follows:

1. Hypothesis 1: The risk model using structured data alone will predict the development of PrUs better than the model based on the Braden Scale.

2. Hypothesis 2: The risk model based on combined structured and NLP data will predict the development of PrUs better than the model based on the Braden Scale.

3. Hypothesis 3: The risk model based on combined structured and NLP data will predict the development of PrUs better than the model based on structured data alone.

### Conceptual Framework

In developing this protocol, we employ the Aggregation, Organization, Reduction, Transformation, Interpretation, and Synthesis (AORTIS) model of understanding clinical summarization in both computer-independent and computer-supported clinical tasks [19]. Using this framework, “clinical summarization” is any act that can be carried out by a health care team member who utilizes patient and clinical information to create a structured data summary, which in turn supports clinical tasks.

In our conceptual model, any or all of the steps to produce a concise and accurate summary could be performed by either a clinician or an automated system. The model was designed to be sequential, with the output from one step providing input into the next, and task dependent, with the content of each step varying based on the clinical task that the summary was designed to support (see Figure 1). In this study, we include many but not all of the steps of the model to employ AORTIS.

**Figure 1 figure1:**
[figure not shown]
The model used to understand clinical summarization in both computer-independent and computer-supported clinical tasks. Info: information.

In AORTIS, data are organized around the specific clinical situation, development of a PrU. This expedites IE and clinical decision making but requires the application of a significant clinical knowledge base. The process of identifying and extracting the necessary data from structured data or text represents activities related to aggregation and organization. The application of NLP programs represents the reduction and transformation of complex text data, which was not readily computable, into structured data elements that could be included in prediction models. The development of prediction models represents the interpretation and synthesis of these data, which could be presented to clinicians for interpretation.

## Methods

### Overview

This is a 5-year longitudinal, retrospective, inception, cohort study targeting veterans with SCI. This research was approved by the Department of Research and Development, James A Haley Veterans’ Hospital, and the VHA Central Institutional Review Board. As described below, the study is ongoing. Each section describes the current status of the study activities as complete, ongoing, or planned.

### Expert Panel—Complete

An expert panel meeting was held in March 2014 to discuss PrU risk factors. The goal of the panel was to identify factors that were likely present in the EHR and could be used to develop improved risk models for PrU development. Participants included two physicians specializing in care for veterans with SCI, three nurse researchers, a wound care specialist, an SCI outcomes registry coordinator, a physical therapist, a dietitian, and a social worker. All members of the expert panel had multiple years of experience in managing persons with PrUs and SCI. Members of the study team also attended the expert panel meeting. Results of the expert panel were iteratively reviewed and refined by two additional physicians and a nurse specializing in research and treatment of PrUs in veterans with SCI.

### Variables Selection and Definition—Ongoing

The dependent variable for this study will be documentation of the occurrence of a PrU in the EHR within 1 year (ie, 1-year incidence risk of PrU). The definition of the presence of a PrU used for case identification is based on ICD-9-CM codes (707.0-707.9) and the application of the classification algorithm based on text analysis or a combination of these two sources, depending on what is found to be more accurate. The potential independent variables for this study include the risk factors that were identified through a literature review and validated by expert panel discussion. The final list of potential risk factors, with input from the expert panel, will be extracted from multiple tables in the EHR, or from semistructured and unstructured text notes, for use in analysis. Three sets of candidate predictors based on data sources will be generated to develop each risk model: (1) structured data extracted directly from the EHR, (2) Braden scores, and (3) a combination of existing structured data and data extracted from text through the NLP processes.

The investigators conducted a comprehensive literature review generating a list of approximately 50 potential independent variables or risk factors (eg, demographics, diseases status, comorbidities, health behaviors, psychosocial factors, and home care). This list was reviewed by the expert panel for logical consistency, completeness, clinical relevance, and whether they were modifiable or not. The panel identified high-priority risk factors and discussed practical considerations including where the risk factor might be located in the EHR, how reliable these data might be, and alternative ways to document risk factors. Subsequently, persistent moisture on the skin, the type of living situation of the patient, evidence of malnutrition, and documentation that the patient took steps to redistribute their weight during the day were targeted as risk factors available in unstructured data. Structured data contained elements of the Braden Scale, lab values, and other variables (see Table 1). Several coding systems are used to classify structured data variables, including the ICD-9-CM, Logical Identifiers Names and Codes (LOINC), and the Healthcare Common Procedural Coding System (HCPCS). International Classification of Diseases, Tenth Revision, Clinical Modification (ICD-10-CM) codes were not implemented in the VHA until after the end of this study and are not used.

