### Sample and Sampling—Complete

Using VHA data in its Corporate Data Warehouse obtained through its Veterans Affairs Informatics and Computing Infrastructure (VINCI), we identified an inception cohort (N=12,344) of veterans with SCI who received care in the VHA in FY 2009, but had no PrU in the 12 months prior to 2009 based on recorded ICD-9-CM codes. This group was considered free of PrUs for the purpose of the study. All structured hospital discharges (N=4090), outpatient encounters (N=5,202,804), and text data (N=9,888,245) for the cohort for FY 2009-2013 (October 1, 2008-September 30, 2013) were obtained through the VINCI. Veterans from this cohort were classified as having a PrU (ie, PrU+) or not having a PrU (ie, PrU-) during the study period based on both structured and text data. A total of 3860 PrUs were identified based on structured data and 829 based on text data alone, resulting in a total incidence of 4689 (4689/12,344, 37.99%) across the study period.

**Table 1 table1:** Risk factors categorized by structured, semistructured, and unstructured data sources.

Data source	Risk factor	Description or definition
Structured	Age	Age in years
	Gender	Male/female
	Race/ethnicity	Race/ethnicity
	Education level	Highest level of education
	VHA^a^ eligibility	VHA category, service connection
	Body weight	Body mass index, most recent weight, or change in weight
	Patient status	Inpatient/outpatient when pressure ulcer develops
	Pattern of preventive care	Consistency of annual well-patient exam
	Cognitive dysfunction	ICD-9-CM^b^ codes (ie, traumatic brain injury, dementia, and Alzheimer’s disease)
	Comorbidities—psychological	ICD-9-CM codes (ie, depression, anxiety, and posttraumatic stress disorder)
	Comorbidities—physical	ICD-9-CM codes (ie, diabetes mellitus, pulmonary disease, cardiac disease, renal disease, peripheral vascular disease, anemia, deep vein thrombosis, cancer, infection, lower extremity fractures, spasticity, autonomic dysreflexia, hypotension, and heterotopic ossification)
	Laboratory analysis	LOINC^c^ codes for lab values (ie, C-reactive protein, white blood cells, erythrocyte sedimentation rate, renal function, hemoglobin, hematocrit, albumin, and prealbumin)
	Medications	VHA formulary to identify chemotherapeutics, steroids, and benzodiazepines
	Surgery	ICD-9-CM codes of surgical procedures within previous 6 months of pressure ulcer development (administrative data)

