### Model Development

An automated model selection procedure will be performed with the R package *glmulti* [26] to select variables and interaction terms in a logistic regression model of PrU status in the training sample. The automated model selection procedure will return a set of *n* best models, ranked by their information criteria values as well as estimating importance scores for the predictors. Thus, it offers us the flexibility to select from the set a more parsimonious or more intuitively reasonable final model that is context based. Another consideration is for the final prognostic model to include variables that could be easily assessed in practice and with minimal burden on the respondent SCI patients. The fully specified prognostic model will eventually be part of an automated decision support system.

The clinical utility of the risk scores will be evaluated for different risk thresholds and the sensitivity, specificity, positive predictive value, and negative predictive value will be included as performance measures in the automated output. In addition, a separate listing of risk factors will be provided for each risk model and ranked by their rounded Z-scores (or standardized regression coefficients). A higher Z-score implies a more “important” contribution of that variable in the model. These lists will assist the clinicians in prioritizing what variables to assess. Each product will be accompanied with appropriate complete operational definitions and scoring instructions.

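### The outcome is defined as 1-year pressure ulcer risk, but the only case classification covers five fiscal years, and the plan does not say which one the logistic model uses

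*Protocol article*

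**What the plan says.** Three places in the protocol article bear on the outcome.

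- **Variables Selection and Definition** makes the dependent variable "documentation of the occurrence of a PrU in the EHR within 1 year (ie, 1-year incidence risk of PrU".
- **Sample and Sampling**, marked complete, reports: "Veterans from this cohort were classified as having a PrU (ie, PrU+) or not having a PrU (ie, PrU-) during the study period". The data were obtained "for the cohort for FY 2009-2013 (October 1, 2008-September 30, 2013", and the count is given as "resulting in a total incidence of 4689 (4689/12,344, 37.99%) across the study period".
- **Data Analysis** and **Model Development**, still planned, split the 12,344 veterans once, 70% to 30%, and select predictors in a "logistic regression model of PrU status in the training sample". Neither section attaches a time horizon to that status.

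The five-year PrU+/PrU- label is the only status that the article defines by an actual classification, and 4689 is the only event count. No 1-year count appears, and nothing explains how a 1-year response would be obtained from the five-year label.

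**The concern.** The same outcome has two horizons. The stated objective is a valid probability of developing a pressure ulcer. Model Development evaluates sensitivity, specificity and predictive values at risk thresholds, and the Discussion foresees using the scores to direct costly preventive resources. All of these depend on the period to which the probability refers.

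If the existing five-year status were modelled, the tool would return five-year probabilities under a 1-year label. The planned Hosmer-Lemeshow test and decile plot could not reveal this. Derivation and validation samples are random parts of one cohort with one label, so a model calibrated to the five-year status would look well calibrated.

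Table 1 adds to the difficulty. Surgery, inpatient or outpatient status, and pain are all timed relative to the ulcer's development. A veteran without an ulcer has no such date, so those definitions do not supply a common starting point for a 1-year window.

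**Working it through.** **Inputs from the article.** Outcome horizon: 1 year. Classification window: five fiscal years. Cases: "A total of 3860 PrUs were identified based on structured data and 829 based on text data alone". Cohort: 12,344. Split: 8641 and 3703. The hazard shape, loss rate, sensitivity, false positive rate and AUC used below are not in the article and are assumptions.

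**1. Reproduce the plan's figures.** 3860 + 829 = 4689, and 4689/12,344 = 0.37986, or 37.99% as stated. 0.7 × 12,344 = 8640.8 and 0.3 × 12,344 = 3703.2, which agree with 8641 and 3703. The split is therefore of veterans, one record each, not of person-years. I take the 4689 as veterans, as the denominator implies.

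**2. Convert to one year under a constant hazard with no losses.** p1 = 1 − (1 − p5)^(1/5) = 1 − (0.62014)^(0.2) = 0.0911. The ratio is 0.37986/0.0911 = 4.17. Expected 1-year cases are 12,344 × 0.0911 ≈ 1125.

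**3. Vary the assumptions.** With a Weibull cumulative hazard, H(5) = −ln(0.62014) = 0.478, H(1) = H(5) × (1/5)^k, and p1 = 1 − exp(−H(1)).

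| Assumption | 1-year risk | Ratio of 5-year to 1-year risk |
|---|---|---|
| k = 0.5 (risk front-loaded) | 19.2% | 1.97 |
| k = 0.7 | 14.3% | 2.65 |
| k = 1 (constant hazard) | 9.1% | 4.17 |
| k = 1.2 | 6.7% | 5.68 |
| Equal counts each year (37.99%/5) | 7.6% | 5.0 |
| Constant hazard, competing loss 3% per year | 9.8% | 3.89 |
| Constant hazard, competing loss 8% per year | 10.9% | 3.49 |
| Structured cases only (3860/12,344 = 31.3%) | 7.2% | 4.33 |

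The competing-loss rows solve h/(h+m) × [1 − exp(−5(h+m))] = 0.37986 for h, and then evaluate the same expression at one year. The range of about 2 to 5.7 belongs to k from 0.5 to 1.2. A more steeply rising hazard goes beyond it (k = 1.5 gives 9.1).

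**4. The ratio is an average.** Under a constant hazard, a veteran with a 5-year risk of 5% has a ratio of 4.9. At 60% it is 3.6, and at 90% it is 2.4.

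**5. Consequences under step 2.**

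- *Predictive value.* For an illustrative classifier with sensitivity 0.60 and false positive rate 0.10, PPV = 0.6p/[0.6p + 0.1(1 − p)]. This is 0.786 at p = 0.380 and 0.376 at p = 0.091.
- *Validation events.* 3703 × 0.37986 ≈ 1407 over five years. 3703 × 0.0911 ≈ 337 over one year.
- *Precision of an AUC of 0.70 (Hanley-McNeil).* The standard error is 0.0091 with 1407 events and 0.0165 with 337.

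**The case against.** The strongest reply is that only Variables Selection and Definition says what will be modelled, and it says one year. Sample and Sampling may simply describe the cohort. The analytic dataset was not yet built, PrU status is compatible with a 1-year definition, and 37.99% is never called the modelled event rate. This stands to a point: use of the five-year label is an inference, and the consequences above are conditional on it. It does not remove the conflict, because no other status or count is given and nothing connects the two.

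A second reply is that the index date and the handling of death and loss belong in a full protocol or analysis plan that is not shown. That is fair, and their absence alone would be no finding. The point is the conflict between two stated horizons.

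A third is that Hypotheses 1 to 3 compare models by AUC and partial AUC in exactly the same veterans. That also stands. A shared label does not by itself invalidate those comparisons, so a reader should not infer that the hypothesis tests fail.

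A reader might also infer that coding veterans who died without an ulcer as PrU- is misclassification that biases the effects of age and comorbidity downward. The document does not support this. For absolute risk with death as a competing event, such a veteran did not have the event. Only departure from VHA care leaves the outcome unobserved, and the article gives no figure for it.

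**Conclusion.** The inconsistency is real and should be settled before the models are fitted, since every predicted probability, predictive value and calibration result depends on the horizon.

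Its size is conditional on the five-year status being the logistic response. In that case the average overstatement of 1-year risk is about 4.2-fold under a constant hazard without losses, and about 2 to 5.7-fold under the other hazard shapes considered. Even the lower end matters for a tool whose product is a probability.

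Two stronger readings go too far. The article does not show that the model will be trained on the five-year label. Nor is fourfold a figure from the article or a multiplier that applies to each veteran.

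**What to change.** Reconcile Variables Selection and Definition, Sample and Sampling, and Model Development to one horizon, and state how the response is built.

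- **If 1-year risk is intended, as stated:** set an index date that applies equally to PrU+ and PrU- veterans. Measure predictors before that date, and derive PrU in the following 12 months from the data already extracted. Report that 1-year event count as the modelled event rate in place of 37.99%. Annual landmarks, with each veteran wholly in derivation or validation and clustered standard errors, are one option among several.
- **If 5-year risk is intended:** relabel the outcome and the tool accordingly, and account for veterans who leave VHA care before five years.

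The cost is wording and re-derivation of one variable while the analysis is still planned. The 1-year route has two drawbacks. Each window holds fewer events (about 337 rather than 1407 in validation under a constant hazard), although stacked landmarks recover part of this. Also, the described extract begins on October 1, 2008, so predictors measured before the index date would need a baseline year within it. Veterans with an ulcer in that year would then drop out of the 12,344.
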